# A preschool-based intervention for Early Childhood Education and Care (ECEC) teachers in promoting healthy eating and physical activity in toddlers: study protocol of the cluster randomized controlled trial PreSchool@HealthyWeight

**DOI:** 10.1186/s12889-019-6611-x

**Published:** 2019-03-07

**Keywords:** Lifestyle intervention, Overweight, Obesity, Prevention, ECEC teachers, Preschool, Toddlers, Dietary intake, Physical activity

## Abstract

**Background:**

Interventions to prevent overweight and obesity in toddlers are needed to minimize health inequalities, especially in migration and lower socio-economic groups. Preschools are identified as important environments for interventions to prevent overweight and obesity. Early Childhood Education and Care (ECEC) teachers in preschools are potential key actors in promoting healthy eating and physical activity. This paper describes the research design of a Dutch preschool-based intervention for ECEC teachers in promoting healthy eating and physical activity in toddlers.

**Methods:**

PreSchool@HealthyWeight concerns a cluster randomized controlled trial on preschools in Amsterdam Nieuw-West, Netherlands. This city district is characterised by inhabitants with a migration background and low socio-economic status. Forty-one preschools, with 115 ECEC teachers and 249 toddlers/parents, were randomly allocated to an intervention or control group. An intervention for teachers will be carried out on intervention locations and consists of modified versions of 2 existing programs: ‘A Healthy Start’ and ‘PLAYgrounds’. In ‘A Healthy Start’, ECEC teachers learn to provide a healthy and active environment for toddlers. The ‘PLAYgrounds for Toddlers’ program, coaches ECEC teachers to stimulate physical activity in the playgrounds of preschools. PreSchool@HealthyWeight aims to evaluate the effectiveness of the intervention after 9 months. Primary outcomes are the teachers’ knowledge, attitude and practices concerning healthy eating and physical activity, and consequently the level of confidence of ECEC teachers in promoting healthy eating and physical activity in toddlers. Secondary outcomes include the Body Mass Index, body composition, dietary intake and physical activity level of teachers and toddlers. In addition, the activating role of ECEC teachers and the physical activity of toddlers on the playgrounds will be evaluated. Lastly, the knowledge, attitude and practices of parents concerning healthy eating and physical activity will be assessed.

**Discussion:**

It is hypothesized that this preschool-based intervention for ECEC teachers improves the knowledge, attitude and practices regarding healthy eating and physical activity, and consequently the level of confidence of ECEC teachers in promoting healthy eating and physical activity of toddlers. The intervention addresses the call for early intervention to prevent overweight and obesity and to minimize health inequalities.

**Trial registration:**

Netherlands Trial Register (NTR): NL5850. Date registered: August 26, 2016.

## Background

Although in high-income countries the increase in the prevalence of overweight and obesity among children seems to level off, the prevalence of excessive weight in children remains high and is higher in urban settings [1]. In the Netherlands, 18% of the children in the 4 largest cities were overweight in 2015 compared to 11% in other parts of the country. This difference is related to the relatively high number of families with a migration background and low socio-economic status in urban surroundings [2]. Even very young children (3 to 4.5 years old) show consequences of health inequalities, and these inequalities widen with increasing age [3–5]. The period between age 2 and 6 is important for the development of adult overweight [6]. Overweight or obese children are more likely to become overweight or obese as adults [7]. Moreover, they have a higher risk of developing non-communicable diseases and psychosocial impairments earlier in life [8]. Unhealthy eating and low physical activity levels are important causes of excessive weight gain [9]. Therefore, interventions to promote healthy eating and physical activity in toddlers are needed, especially in migration and lower socio-economic groups to minimize health inequalities.

In the Netherlands, urban preschools provide an opportunity to reach many toddlers and their parents, particularly those with a migration background or low socio-economic status. When a toddler is at risk for language or developmental delays, parents are advised to enrol their toddler in a preschool that provides play-based education. These preschools prepare children for primary school [10]. Toddlers spend up to 15 h per week in preschool and preschools are therefore identified as important environments for interventions to prevent overweight and obesity in young children [11].

Early Childhood Education and Care (ECEC) teachers in preschools are potential key actors for promoting healthy eating and physical activity in toddlers. ECEC teachers may set a healthy example and be positive role models in healthy eating and physical activity behaviours [12, 13]. In the light of this potential role, the knowledge, attitude and practices regarding healthy eating and physical activity, and consequently the level of confidence of ECEC teachers in promoting healthy eating and physical activity in toddlers is of interest.

Literature on the role of ECEC teachers in promoting healthy eating and physical activity among young children is inconclusive. Ward et al. describe in a systematic review that the effect of specific practices of childcare educators on healthy eating and physical activity in young children is not clear because of the lack of high-quality intervention trials. The authors give recommendations for future research, among which to study previously assessed practices of educators on more diverse populations [14]. Furthermore, Wolfenden et al. emphasizes in a Cochrane review that further research is needed for successful strategies to improve childcare service staff knowledge and attitudes regarding healthy eating and physical activity and to find out more about the effect of such strategies on child physical activity and weight status [15]. Our study, PreSchool@HealthyWeight (PS@HW), involves preschools in Amsterdam Nieuw-West, the Netherlands. Amsterdam Nieuw-West is characterised by inhabitants with a migration background and low socio-economic status. PS@HW intends to contribute to evidence-based best practices for ECEC teachers in diverse populations.

The primary objective of PS@HW is to increase the knowledge, attitude and practices of ECEC teachers regarding healthy eating and physical activity, and consequently the level of confidence in promoting healthy eating and physical activity of toddlers. The secondary objective is to gain insight in the effect of the preschool-based intervention on:Body Mass Index (BMI) and body composition of ECEC teachers and toddlers;dietary intake and physical activity levels of ECEC teachers and toddlers;the activating role of ECEC teachers regarding physical activity of toddlers on the playground;amount and type of physical activity in toddlers on the playground;motor development of toddlers;knowledge, attitude and practices of parents regarding healthy eating and physical activity of toddlers;weight perception of parents concerning the weight status of their toddler.

## Methods

### Study design and setting

PS@HW concerns a cluster randomized controlled trial. Preschools of child care organization Impuls in Amsterdam Nieuw-West, the Netherlands, were randomly allocated to an intervention or control group by an independent researcher (with the use of computer-generated randomization lists). The study period is 9 months, starting with baseline measurements and ending with close-out measurements. For ECEC teachers, additional data will be collected after 4 months of follow-up. After the baseline measurements, a preschool-based intervention regarding healthy eating and physical activity will be carried out on preschools in the intervention group. The intervention consists of modified versions of 2 existing Dutch programs for ECEC teachers: ‘A Healthy Start’ (Dutch: Een Gezonde Start) and ‘PLAYgrounds’. Figure 1 provides a schematic overview of the study.

**Fig. 1 Fig1:**
[figure not shown]
Schematic overview of the study

### Recruitment

In total, 42 preschools of child care organization Impuls were available for allocation. One location was excluded because of practical reasons and 4 preschools were combined in the allocation as they shared a building or playground. The final sample includes 41 preschools, in which 115 ECEC teachers and 249 toddlers and their parents were recruited. ECEC teachers who worked at multiple preschool locations were excluded. Toddlers and their parents were included if the toddler was 2.5 to 3.5 years old. ECEC teachers and parents received oral and written information about the study. For ECEC teachers, information meetings were organized. Parents were individually approached by the research staff. All participating ECEC teachers and parents gave written informed consent. Parents gave additional written informed consent for their toddlers.

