#### PLAYgrounds for Toddlers

The initial ‘PLAYgrounds’ program concerns a physical education based playground program for primary schools to improve physical activity levels of children during recess times. The program consists of a multi-component alteration of the schools’ playground. In addition, the playground usage is stimulated by altered time management of recess times, teachers stimulating physical activity and a modification of the physical education content. ‘PLAYgrounds’ is proven to be effective in primary schools [17, 18]. For PS@HW, the program was adapted to the context and target group on preschools of child care organization Impuls. This ‘PLAYgrounds’ program for toddlers focusses on the amount and type of physical activity and the prompts of ECEC teachers within the possibilities of the outdoor space and availability of material in preschools. Two training sessions and 1 evaluation session will be organized for in total 4 groups of ECEC teachers. In addition, a trainer will visit each preschool in the intervention group between the training sessions to give specific instructions for improvement (coaching on the job) to the local team of ECEC teachers.

In PS@HW, ‘A Healthy Start’ and ‘PLAYgrounds for Toddlers’ have a complementary role. The multi-component and multilevel programs share a focus on providing a healthy and active environment for toddlers and the role of ECEC teachers to set a healthy example. The interventions will be applied consecutively, in order not to overload ECEC teachers. Attendance records will be used to determine the adherence of ECEC teachers to the intervention. All participants who will attend at least 2 meeting of ‘A Healthy Start’ and 1 meeting of ‘PLAYgrounds for Toddlers’ will receive certificates.

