### Procedures and outcome measures

ECEC teachers and parents will be asked to fill in a questionnaire at baseline, 4 months follow-up (only applicable for ECEC teachers) and 9 months follow-up (close-out). At the same time, anthropometric measurements in ECEC teachers and toddlers will be carried out. Furthermore, observations on the playgrounds will be performed at 4 and 9 months follow-up. The questionnaire for ECEC teachers includes questions on knowledge, attitude and practices regarding healthy eating and physical activity, and questions on the level of confidence in promoting healthy eating and physical activity in toddlers. For parents, the questionnaire includes questions on knowledge, attitude and practices regarding healthy eating and physical activity of their toddler. In addition, ECEC teachers and parents will be asked to fill in a 3-day food and physical activity record at baseline and 9 months follow-up (parents fill in the records for their toddler).

All measurements will be carried out by trained research staff and students of the Amsterdam University of Applied Sciences using Standard Operation Procedures. The study team is coordinated by 3 unblinded researchers ([name]) and 1 blinded researcher (MS).

Questionnaires, score forms and records will be coded to protect the privacy of the participants. Data from paper questionnaires and score forms will be handled into Microsoft Excel by double data-entry. Records will be entered in Microsoft Excel and checked by trained research staff and students of the Amsterdam University of Applied Sciences.

Table 1 provides a summary of the outcome measures for the study timepoints.

**Table 1 Tab1:** Summary of the outcome measures for the study timepoints

TIMEPOINT	BASELINE			4 MONTHS					9 MONTHS		
	ECEC*	Toddlers	Parents		ECEC*	Toddlers	Parents		ECEC*	Toddlers	Parents
OUTCOME MEASURES											
*Demographic data*	X	X	X								
*Knowledge of Dutch food-based dietary guidelines*	X		X		X				X		X
*Attitude about healthy eating and physical activity*	X		X		X				X		X
*Food and activity practices*	X		X		X				X		X
*Level of confidence in promoting healthy eating and physical activity*	X				X				X		
*Anthropometry and body composition*	X	X			X				X	X	
*Dietary intake*	X	X							X	X	
*Physical activity level*	X	X							X	X	
*Role (prompts) on playground*					X				X		
*Amount and type of physical activity on playground*						X				X	
*Motor development*		X								X	

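### Toddlers older than 3.25 years at inclusion turn 4 before the 9-month close-out; the protocol gives no age of transfer to primary school, and its toddler model has no age term

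*Protocol article*

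**What the plan says.** Under Recruitment, the protocol article says: "Toddlers and their parents were included if the toddler was 2.5 to 3.5 years old". It gives the sample as follows: "The final sample includes 41 preschools, in which 115 ECEC teachers and 249 toddlers and their parents were recruited". Study design and setting fixes the follow-up: "The study period is 9 months, starting with baseline measurements and ending with close-out measurements".

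Table 1 places toddler anthropometry, dietary intake, physical activity level and motor development at baseline and 9 months. On the playground, "observations on the playgrounds will be performed at 4 and 9 months follow-up". Motor testing applies only above 3.0 years of age.

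On the setting, the Background says: "These preschools prepare children for primary school". It gives no age at which children transfer. On delivery, the section on PLAYgrounds for Toddlers says: "The interventions will be applied consecutively, in order not to overload ECEC teachers". No end date is given for either program.

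The planned analysis is a mixed model with time, treatment and their interaction as fixed factors, and subject and location as random factors. It is meant for teachers, toddlers and parents alike. Age is not in the model, although date of birth is collected and toddlers' age is to be calculated in months.

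**The concern.** The age window and the length of follow-up are both fixed, and together they take part of the toddler sample past the fourth birthday while the trial is running. If children move to primary school at about that age, the oldest leave the setting in which the intervention works.

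Two things could follow for a leaver. The 9-month value may be missing, which costs precision; the missingness would be driven by age, which the stated model omits. Or the value may be taken after the child has left, which dilutes any effect because the last weeks were spent elsewhere. The outcomes at stake are the toddlers' secondary outcomes. The 9-month playground observation is the clearest case, since it can only include children still attending.

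**Working it through.** The protocol gives no transfer age, no toddler attrition figure and no required sample size for toddlers, so there is no figure of its own to reproduce.

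**Inputs from the protocol.** Age at inclusion 2.5 to 3.5 years; follow-up 9 months = 0.75 year; 249 toddlers in 41 preschools; ICC 0.05 (Planned statistical analysis); motor test above 3.0 years.

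**Assumptions.** Transfer age 4.0 years, varied below. Ages evenly spread over the window, varied below. The ICC of 0.05 holds for toddler outcomes; it is stated alongside a mean cluster size of 3, which fits teachers (115/41 = 2.8) rather than toddlers (249/41 = 6.1).

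**Step 1: age at close-out.** 2.5 + 0.75 = 3.25 and 3.5 + 0.75 = 4.25 years. A toddler turns 4 before close-out if older than 4.0 − 0.75 = 3.25 at inclusion. The oldest turns 4 at (4.0 − 3.5) × 12 = month 6. At 4 months the oldest is 3.5 + 4/12 = 3.83, so nobody has reached 4 by then.

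**Step 2: number concerned.** Share = (4.25 − transfer age)/(3.5 − 2.5), with a minimum of zero.

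| Assumed transfer age | Share (even spread) | Toddlers of 249 |
|---|---|---|
| 4.0 | 25% | 62 |
| 4.1 | 15% | 37 |
| 4.25 or later | 0% | 0 |

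At 4.0 years, a linear skew toward the young end gives 0.25² = 6% (about 16 toddlers), and toward the old end 1 − 0.75² = 44% (about 109). The result therefore depends on the actual ages, which the trial holds.

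**Step 3: time outside the setting.** At 4.0 years, leavers lose between 0 and 3 of the 9 months, on average 1.5 months under even spread.

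**Step 4: precision if every leaver is lost.** For a comparison of means, the standard error is proportional to √(design effect/N), with design effect = 1 + (N/41 − 1) × 0.05.
- N = 249: 6.07 per preschool, design effect 1.254.
- N = 249 − 62 = 187: 4.56 per preschool, design effect 1.178.
- Ratio: √[(1.178/187)/(1.254/249)] = √1.25 = 1.12, a rise of about 12%.

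Ignoring clustering gives 1/√0.75 = 1.155, or 15%, which overstates the loss: with fewer toddlers per preschool the design effect falls too.

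**Step 5: motor development.** Only toddlers above 3.0 at inclusion can have a baseline score: under even spread, 0.5 × 249 = about 125. Of these about 62, or half, are above 3.25. Motor change is therefore the outcome most exposed to leaving at 4.0, and the one most reduced by an analysis restricted to 3.25 years or younger.

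**The case against.** The strongest objection is that the decisive premise is not in the document. No transfer age is given, nothing says that children leave during follow-up, and at 4.25 years or later nobody is affected. A reader might infer that the age window simply does not fit the study period, or that it was set without regard to follow-up. The protocol supports neither; the misfit is conditional.

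A reader might also infer that the oldest children miss part of PLAYgrounds. The program follows the other one and is bracketed by the two playground observations, but it consists of teacher sessions and coaching visits with no stated end date, and could be finished before month 6. What leavers would lose is time in the setting, not demonstrably a program component.

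Nor can all close-out data be assumed lost. Only the playground observations are tied to the preschool. The weighing scale and stadiometer are portable, no place is stated for the other toddler measurements, and parents complete the questionnaires and 3-day records without the child having to attend.

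Setting 25% against the 10% drop-out allowance is tempting but unsound, because that allowance belongs to a calculation whose cluster size fits teachers.

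Finally, age precedes treatment and is unlikely to differ much by arm, so loss by age alone would bias the comparison only if the effect varied with age. Some outcomes, such as the BMI z-score, are already standardised. Detail on leavers may also stand in a fuller document.

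All of this stands, and it limits the point. It does not remove the age arithmetic, or the fact that the stated toddler model omits a variable that is already collected and would drive any such loss.

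**Conclusion.** The point holds in conditional form. It is certain that toddlers older than 3.25 years at inclusion turn 4 between months 6 and 9. Whether they leave preschool depends on a transfer age that the protocol does not give.

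If transfer is at 4.0 years and ages are evenly spread, about 62 of 249 toddlers may leave before close-out; the figure falls to 37 at 4.1 years and to none at 4.25 or later. Leavers would miss the 9-month playground observation and up to the last 3 months in the setting. Their other close-out values may be missing or taken after leaving. The 12% rise in standard error is an upper figure for this scenario: it needs every such child to be lost and an ICC of 0.05.

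The consequence is lost precision and some dilution in secondary toddler outcomes. A reading of serious bias between arms is not supported, and the teacher primary outcomes are untouched.

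**What to change.** 1. **Model.** Add baseline age in months and its interaction with time to the toddler mixed models. Age-related loss is then handled through a variable in the model. Date of birth is already collected, so this costs nothing and is worthwhile whatever the transfer age.
2. **Sensitivity analysis.** State the transfer age and how many toddlers reach it before month 9, and repeat the toddler analyses in those who do not: 3.25 years or younger at baseline if transfer is at 4.0. The subset is fixed by a baseline value, so it is free of selection by arm. The cost is a sample of about 187 and the loss of about half of the toddlers with a baseline motor score (62 of 125); the motor result should be read accordingly.
3. **Leavers.** Follow children who leave before close-out by one rule applied equally in both arms, and record the actual measurement date. The cost is some scheduling work and, if measurements are brought forward, some values that fall before month 9.

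No change to the upper age limit is proposed. Recruitment is complete, and a limit of 3.25 years would have halved the toddlers with a baseline motor score.

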### Intervention

The preschool-based intervention for ECEC teachers consists of modified versions of the programs ‘A Healthy Start’ and ‘PLAYgrounds’.

#### A Healthy Start

The national program ‘A Healthy Start’ is an initiative of the Dutch Ministry of Health, Welfare and Sport and the Ministry of Social Affairs and Employment. It is developed by 7 renowned Dutch knowledge centres (Knowledge Centre for Sports Netherlands, Netherlands Youth Institute, Pharos Dutch Centre of Expertise on Health Disparities, the Netherlands Nutrition Centre, National Institute for Public Health and the Environment, the Netherlands Organisation for applied scientific research TNO, and VeiligheidNL). Train-the-trainer courses are organized for ECEC teachers and ECEC teachers in training. ‘A Healthy Start’ focusses on the development of knowledge and practices about nutrition, physical activity and education of ECEC teachers. The national program consists of a basic model and 4 in-depth modules. The basic module includes 3 face-to-face meetings of 2.5 h each. The in-depth modules, each between 4 and 6 h, are optional and concern the themes Nutrition, Physical Activity, Weight and Safe Behaviour & Safe Environment. Special attention is given to the diversity of children and their parents [16]. For the intervention of PS@HW, research staff and 3 coaches of child care organization Impuls, who met criteria of the train-the-trainer course for the national program, composed a modified version of ‘A Healthy Start’. The modified version includes theory and practical assignments of the basic module and in-depth modules Nutrition, Physical Activity and Weight. Three face-to-face meetings of 2 h will be organized for 8 groups of ECEC teachers (in total 24 meetings). Each meeting will be led by a coach of child care organization Impuls and a member of the research staff. In the first meeting ECEC teachers will reflect on their own lifestyle and on the topic healthy lifestyle in their organization. Furthermore, theory about the Dutch food-based dietary guidelines (2015) will be discussed. The second meeting focusses on the interaction with toddlers and a healthy lifestyle, and the role of ECEC teachers in setting a healthy example. In the third meeting, the interaction with parents and a healthy lifestyle will be discussed.

